#### Phone surveys

The phone survey analyses will principally aim to determine the reliability of the phone survey tools. Reliability analyses will aim to determine the stability and consistency of results [11]. A Cronbach’s alpha of 0.7 or higher is proposed as the cutoff for determining sufficient evidence of reliability [11]. Additional analyses related to the internal consistency of the scale as well as the presence of floor and ceiling effects will be conducted and overall findings summarized in an overarching table on validity and reliability [11].

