Study aim 2*	Phone survey for pregnant women: RMC during pregnancy	Women 5–7 months pregnant in four districts of MP	880 women interviewed as part of face to face surveys contacted to yield 146 completed face to face and phone survey interviews	• 20% phone survey response rate • Proportion of positive responses of 0.35 for rater 1 and 0.40 for rater 2
Study aim 2	MCTS/RCH registration	• FLHWs • Block and district medical officers • Data entry officers	64 in-depth interviews, 24 focus group discussions, and 24 observations	
Study aim 4	User perceptions of Kilkari	• FLHWs: ASHAs, ANMs • Women enrolled to Kilkari and male phone owners	49 in-depth interviews and six focus group discussions	

*Sample estimates based on kappa of 0.80, alpha of 0.05, margin of error of 0.05%

Among pregnant women, a module on RMC during antenatal care will be integrated into the baseline assessment amongst the enrolled women. To measure RMC during childbirth, a total of 880 women with a birth outcome in the preceding 1 to 4 months will be interviewed. This sample size was designed to accommodate inter-modal testing and is sufficient to additionally measure the prevalence of the RMC indicator of reported verbal abuse during childbirth with 80% power, alpha of 0.05, and precision of 5%.

To generate validated phone survey tools for RMC, we will aim to determine the inter-modal reliability of face to face versus computer-assisted telephone interviewing (CATI)/phone surveys for both pregnant and postpartum women. Assuming a kappa of 0.80, a margin of error of 0.05, an alpha of 0.05, and the proportion of positive responses of 0.35 for rater 1 and 0.40 for rater 2, 146 participants who have completed the survey are required. Adjusting for a 20% loss to follow-up between the face to face women’s survey and the following mobile phone survey, and a 20% baseline completion percentage for the latter, 880 women with a birth outcome in the preceding 1 to 4 months will be interviewed face to face. Within 1–2 weeks of the initial interview, a random sample of those completing the face to face interview who consent to be called for the follow-up phone survey will be contacted. Assuming a 20% response rate, all 880 women will be contacted as part of the phone survey to yield the 146 completed face to face and phone survey interviews.

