#### Study aim 1: Generate evidence on the effectiveness of Kilkari in four districts of MP

Knowledge attitudes and practices (KAP) surveys will be administered at baseline and endline containing modules on phone ownership, geographical and demographic characteristics, knowledge (danger signs during pregnancy, delivery, and postpartum; essential newborn care; nutrition; hygiene, diarrhea treatment, family planning, etc.), practices (immediate, early, and exclusive breastfeeding; complementary feeding; skin-to-skin care, etc.), RMC, and coverage for antenatal care, delivery, and postnatal care. Questions on exposure to and sources for health information content will additionally be asked to identify possible sources of contamination. The list of individuals randomized to receive Kilkari content will be provided to BBC Media Action for enrollment into Kilkari continuously throughout the implementation of the baseline survey. Following 11–12 months, participants from both study arms will be interviewed as part of the face to face endline survey.

A phone survey will be administered to all study arm participants on a rolling basis at 1 month postpartum to measure RMNCH practices, including infant feeding practices and essential newborn care as well as RMC. Methods to generate a validated phone survey tool are described elsewhere and in brief will include a face to face survey administered to women during pregnancy and with a live birth outcome in the preceding 1–4 months postpartum at the time of the household listing. A sub-sample of respondents from the initial face to face survey will be administered a second test-retest survey by a separate but similar profile of enumerator. Findings from the face to face surveys will be used to generate phone survey tools which will be implemented amongst a random sample of pregnant and postpartum women who consent to be called for the follow-up phone survey. Analyses to assess the intermodal reliability of face to face versus phone survey responses will be used to generate a validated tool. The tool developed for postpartum women will subsequently be administered to women enrolled into the iRCT during pregnancy at 1–4 months postpartum (Fig. 2).

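### The only stated reliability cutoff for the phone tools is Cronbach's alpha of at least 0.7, but the validation sub-study is aimed at, and sized for, paired agreement (kappa 0.80)

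*Protocol article*

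**What the plan says.** The Phone surveys subsection of Analyses in the protocol article gives the purpose: "Reliability analyses will aim to determine the stability and consistency of results". It then sets its single pass mark: "A Cronbach’s alpha of 0.7 or higher is proposed as the cutoff for determining sufficient evidence of reliability". Further work on internal consistency and on floor and ceiling effects is listed after that, with everything summarised in one table. The subsection names no agreement statistic.

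The target of the validation is set elsewhere in the article:

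- Sampling: "we will aim to determine the inter-modal reliability of face to face versus computer-assisted telephone interviewing (CATI)/phone surveys for both pregnant and postpartum women". The sizing there begins "Assuming a kappa of 0.80, a margin of error of 0.05, an alpha of 0.05" and continues "the proportion of positive responses of 0.35 for rater 1 and 0.40 for rater 2, 146 participants who have completed the survey are required".
- Table 2, aim 1c: a test-retest component of 168 women, each interviewed twice, with the same positive-response proportions and a footnote giving kappa 0.80.
- Measurement, study aim 1: "Analyses to assess the intermodal reliability of face to face versus phone survey responses will be used to generate a validated tool". The same paragraph plans a second interview by a separate enumerator. It also says that the methods for generating the tool are described elsewhere.

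**The concern.** Stability and inter-modal reliability concern whether the same woman gives the same answer on a second occasion or in another mode. They can be judged only from paired answers. Cronbach's alpha, as usually computed, is a property of one administration and shows how far the items move together within it. The printed cutoff therefore tests something other than what the sub-study was built to estimate.

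Alpha also presupposes a scale. A set of respectful-care items may form one. Breastfeeding and newborn-care practices are separate behaviours, and the article gives no reason to treat them as measures of a single construct.

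At stake are objective 1c (validated phone tools) and the reading of the later phone survey. The Measurement section plans that survey until 3500 women are reached (1750 per arm), to assess breastfeeding and newborn care.

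**Working it through.** **1. The plan's own figure.** The inputs from Sampling are kappa 0.80, positive proportions 0.35 and 0.40, margin of error 0.05, and alpha level 0.05 (taken as two-sided, z = 1.96).

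- Chance agreement: 0.35 × 0.40 + 0.65 × 0.60 = 0.53.
- Observed agreement: 0.80 × (1 − 0.53) + 0.53 = 0.906.
- The large-sample (Fleiss-Cohen-Everitt) variance factor for this 2×2 table is Q = 0.3804, and n = z² × Q / d².
- With d = 0.05: 3.8416 × 0.3804 / 0.0025 ≈ 585.
- With d = 0.10: 3.8416 × 0.3804 / 0.01 ≈ 146.

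The stated 146 is thus a sample size for estimating kappa, with a half-width of about 0.10 rather than the printed 0.05. That discrepancy is a separate matter. What counts here is that the sizing statistic is kappa. The test-retest figure follows from it: 146 × 1.15 = 167.9, or 168.

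**2. What alpha responds to.** For k standardised items with mean inter-item correlation r, alpha = k × r / (1 + (k − 1) × r). The article gives neither k nor r, so the values below are assumptions.

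| k | r | Calculation | Alpha | Against 0.7 |
|---|---|---|---|---|
| 8 | 0.30 | 2.40 / 3.10 | 0.774 | passes |
| 5 | 0.35 | 1.75 / 2.40 | 0.729 | passes |
| 8 | 0.10 | 0.80 / 1.70 | 0.471 | fails |

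No between-mode term enters. The first two rows pass at any kappa from 0 to 1, and the third fails even if phone and face-to-face answers are identical.

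**3. Simulation at the planned size.** There were 146 women, binary items driven by one factor, positive proportions 0.35 and 0.40, the two modes generated independently (item kappa about 0), and 500 runs per setting. Item counts and loadings are assumptions.

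| Items | Loading | Mean alpha (phone) | Runs with alpha at least 0.7 |
|---|---|---|---|
| 5 | 0.60 | 0.60 | 1% |
| 5 | 0.75 | 0.75 | 89% |
| 10 | 0.60 | 0.75 | 92% |
| 10 | 0.75 | 0.86 | 100% |
| 20 | 0.60 | 0.86 | 100% |

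Agreement is absent in every row, yet the pass rate runs from 1% to 100%. The result follows item number and loading.

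**4. The other possible reading of alpha.** Suppose alpha were computed with the two modes as two items. Then alpha = 2 × (1 − v / (v + 2c)), where v = 0.35 × 0.65 + 0.40 × 0.60 = 0.4675 and c is the between-mode covariance. At kappa 0.54, observed agreement is 0.54 × 0.47 + 0.53 = 0.7838. The both-positive cell is (0.7838 − 1 + 0.75) / 2 = 0.2669, so c = 0.2669 − 0.14 = 0.1269. Alpha is then 2 × (1 − 0.4675 / 0.7213) = 0.70. On this reading agreement does count, but the cutoff would sit at a kappa of about 0.54, against a design value of 0.80.

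**The case against.** The strongest reply is that agreement is not ignored. The article sizes the sub-study on kappa, plans paired and test-retest interviews, and says that the inter-modal analyses feed into the tool. Nowhere does it say that a tool is accepted on alpha alone. It also says twice, in the Background and under study aim 1, that fuller methods are given elsewhere, so an agreement threshold may exist there. All of this stands. It rules out any claim that agreement will go unexamined, and the absence of a kappa threshold from a condensed article is not in itself a fault. What remains is that the Phone surveys subsection does state a criterion for sufficient evidence of reliability, and that criterion does not fit the aim.

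A second reply is that zero agreement between interviews one to two weeks apart is an extreme case, and that item counts and correlations are not in the documents. That is correct. The figures show what alpha depends on. They do not predict how these tools will perform.

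A reader might also infer that the trial's main result rests on a tool passed in this way. The documents do not support that. Table 2 calls the phone survey of enrolled women descriptive and plans the infant-feeding comparison face to face. Both arms also have a face-to-face endline covering practices in pregnancy, around birth and postpartum.

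**Conclusion.** The point holds as a mismatch between a stated criterion and its purpose. The only printed cutoff is for internal consistency, while the sub-study is designed and sized for agreement. As the subsection reads, alpha of at least 0.7 is enough to call a tool reliable, and nothing stated lets poor agreement fail it. Under plausible but assumed item sets, alpha passes or fails regardless of agreement: 0.77 and 0.73 at any kappa, and 0.47 with perfect agreement.

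This rests on the usual reading of alpha, computed within one administration. The alternative across-mode reading still gives a bar well below the design kappa. The consequence is confined to the validation claim and to the phone-survey results. No effect on the primary comparison is shown. The conclusion would soften to a need for alignment if the separate methods document sets an agreement threshold.

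**What to change.** In the Phone surveys subsection, or in the analysis plan that replaces it:

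- Base the reliability criterion on the statistic used for sizing: per-item kappa, face-to-face against phone and test-retest, each with a 95% confidence interval and a minimum fixed in advance.
- Report the paired difference in prevalence (McNemar) for each item, to detect a shift between modes.
- Use an intraclass correlation for any summed respectful-care score.
- Keep Cronbach's alpha only to describe the internal consistency of multi-item scales.
- If an agreement threshold already exists in the separate methods document, cite it and bring this subsection into line with it.

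Choose the minimum with the available precision in mind. With 146 pairs and kappa 0.80, the two-sided 95% half-width is 1.96 × √(0.3804 / 146) = 0.10, an interval of about 0.70 to 0.90.

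The paired interviews are already planned, so the cost is wording, with no added data collection.

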#### Economic evaluation

A full health-economic analysis will only be performed after completion of the main trial. Once costs and effects are estimated, uncertainty analyses, including one-way and probabilistic sensitivity analyses, will be conducted. The latter will be carried out in Microsoft excel using a Monte Carlo simulation with 1000 iterations per analysis. The resulting mean point estimate will be obtained by dividing mean costs by mean effects, while a 95% confidence interval for the ICER is presented based on percentiles. A cost effectiveness plane and cost effectiveness acceptability curve will be used to calculate the probability that the intervention will be cost-effective for each of a number of standard thresholds of cost-effectiveness. Cost-effectiveness will ultimately be determined according to thresholds set forth by the Commission for Macroeconomics and Health and WHO which stipulate that an intervention is “highly cost-effective” and “cost-effective” interventions at one and three times, respectively, the value of per capita gross domestic product per DALY averted. To facilitate comparison with alternative resource uses, we will additionally compare findings against those available in the literature.

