### Sampling

Table 2 summarizes the sample size requirements by activity, along with underpinning assumptions. To determine changes in RMNCH knowledge, practices, and careseeking over time (study aim 1), sampling will be powered to detect changes in coverage across study arms. To detect a 5% difference in reported practice of exclusive breastfeeding assuming an alpha of 0.05, 80% power, the estimated sample size for a two-sample proportions test would be 3200 women. After adjusting for a design effect (variance inflation factor) of 1.25 due to clustering at the level of the Community Development Block and a 20% loss to follow-up from enrollment to endline surveys and a potential loss of 35% of women due to poor reporting of phone numbers and/or changes to original phone numbers provided, a total of 5000 women will be enrolled to the study. Assuming 40% of women have access to a mobile phone, we anticipate that nearly 700,000 households will be listed in all four districts of MP.

**Table 2 Tab2:** Sample size estimates by study aim

Study aim	Survey	Target population	Sample size	Assumptions
Study aim 1a*	Face to face survey to measure changes in infant feeding practices	Women 5–7 months pregnant in four districts of MP	5000	• 5% change in reported practice of immediate and exclusive breastfeeding • Loss to follow-up of 20% from enrolment to final follow-up visit • Variance inflation factor of 1.25
Study aim 1b	Phone survey to measure changes in infant feeding	Postpartum women randomized to Kilkari	5000	Descriptive survey; administered to all women enrolled into the study
Study aim 1c*	Test-retest	Women 5–7 months pregnant in four districts of MP	168 women to be interviewed twice	• Proportion of positive responses of 0.35 for rater 1 and 0.40 for rater 2 • Adjusting for a 15% loss to follow-up/refusal between the first and second surveys
Study aim 1*	Phone survey for postpartum women: infant feeding, essential newborn care, RMC during childbirth	Women 1–4 months postpartum in two districts of MP	880 women interviewed as part of face to face surveys contacted to yield 146 completed face to face and phone survey interviews	• 20% phone survey response rate • Proportion of positive responses of 0.35 for rater 1 and 0.40 for rater 2

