#### Study aim 5: Determine the value for money of Kilkari in four districts of MP

To measure the economic costs of Kilkari we will prospectively measure program, user, and health system costs in the four districts of MP. Program costs associated with the development, start-up, and implementation of program activities will be assessed using an ingredients approach for the 2018–2019 analytic time horizon. Costs to users will be assessed through face to face household surveys and include direct (out of pocket costs for drugs, supplies, consultation fees, transportation) and indirect (wages lost, child care) costs incurred by users for RMNCH careseeking. Finally, we will explore the feasibility of measuring incremental costs to the health system above and beyond those captured by the measurement of program and user costs. Collective consideration of program, user, and health system costs will allow for a societal perspective to be taken and thus a more comprehensive estimate of the full economic costs associated with the program across study arms of individuals exposed versus those not exposed to Kilkari. To measure the incremental effectiveness of Kilkari, data on changes in coverage for RMNCH careseeking and practices assessed through household surveys will be inputted into the Lives Saved Tool to generate a measure of lives saved associated with program activities. Lives saved will be used to yield an estimate of the incremental DALYs averted and ultimately a cost per DALY averted for Kilkari.

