These findings reinforce the need to collect evidence not only on summative evaluation findings, but also on the processes which underpin them. In the case of MOTECH, missing data prevented the measurement of outcome level indicators. Hypothetically, however, had we been able to measure these and assumed target constituents received and listened to messages without measuring exposure, we likely would not have seen an effect and thus concluded that exposure to maternal messages does not influence behavior in the study setting of Ghana. In reality, while it is likely that limited exposure to the program due to technological limitations in message delivery would have eroded any chance for outcome level metrics to be attained, we do not have enough evidence to draw conclusions beyond those highlighting limitations in program reach and exposure. The advantage in having digital health data is that we *can* measure exposure at an individual level and thus if designed appropriately link that with outcome level data. We propose employing the same strategy for assessing Kilkari and thus collecting data on the underlying technological and behavioral performance of the program. We hope that this approach promotes a new standard with regard to linking data on individual level exposure to health outcomes.

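### The percentile interval planned for the cost per DALY averted misorders simulated draws with no benefit, so its limits mislead when the simulated DALY effect straddles zero

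*Protocol article*

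**What the plan says.** The Economic evaluation section of the protocol article plans a "Monte Carlo simulation with 1000 iterations per analysis". On the point estimate it says: "The resulting mean point estimate will be obtained by dividing mean costs by mean effects". On uncertainty it says that "a 95% confidence interval for the ICER is presented based on percentiles". It does not say how draws with a zero or negative effect are ordered, and it names neither Fieller limits nor net benefit.

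Two further displays are planned: "A cost effectiveness plane and cost effectiveness acceptability curve will be used to calculate the probability that the intervention will be cost-effective". The decision rule is separate from the interval: "Cost-effectiveness will ultimately be determined according to thresholds set forth by the Commission for Macroeconomics and Health and WHO", that is, one and three times GDP per capita per DALY averted.

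The denominator is described under Study aim 5. Changes in coverage and practices go into the Lives Saved Tool, after which "Lives saved will be used to yield an estimate of the incremental DALYs averted and ultimately a cost per DALY averted for Kilkari". Objective 5c sets the comparator as no messages. The probability distributions of the simulated costs and effects are not given.

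**The concern.** A cost-effectiveness ratio has no natural order once the effect can change sign. If the programme costs more, which is likely against a comparator of no messages, a draw with a small harm has a large negative ratio. Plain sorting puts that draw below the best draws, although it is the worst kind of result. Draws just above zero effect give very large positive ratios. Percentiles of the mixture no longer run from most to least favourable.

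The stake is how a headline policy figure is read. A negative lower limit invites the reading that Kilkari may save money, and a finite upper limit suggests a bound on the cost per DALY that the data do not support. Both occur when the evidence of benefit is weakest.

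**Working it through.** The article states no ratio, interval or share of negative draws, so there is no figure of its own to reproduce here.

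**Step 1: when the order fails.** Assume normal draws centred on the modelled effect, with z = estimate / SE, and positive incremental cost. Then P(draw < 0) = Φ(−z), and Φ(−1.96) = 2.5%. Below z = 1.96 more than 2.5% of ratios are negative, so the 2.5th percentile must be negative.

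**Step 2: what the limits become.** Simulation with 1,000,000 draws per row: effect N(z, 1) and incremental cost N(1, 0.1), in arbitrary units. The 10% cost SE is an assumption. The last column ranks negative-effect draws as worst.

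| z | draws below 0 | plain percentiles | negative-effect draws ranked worst |
|---|---|---|---|
| 1.0 | 15.8% | −9.2 to 10.3 | 0.33 to unbounded |
| 1.5 | 6.7% | −4.3 to 5.9 | 0.28 to unbounded |
| 1.9 | 2.9% | −1.3 to 3.4 | 0.25 to unbounded |
| 2.0 | 2.25% | 0.19 to 3.0 | 0.24 to about 23 |
| 2.8 | 0.25% | 0.20 to 1.14 | 0.20 to 1.19 |
| 4.0 | 0.0% | 0.16 to 0.50 | 0.16 to 0.50 |

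Fieller limits agree with the last column where they are finite: 0.24 to about 25 at z = 2.0, and 0.20 to 1.20 at z = 2.8. Distortion is therefore already large at z = 2.0. With 1000 iterations, as planned, 26% of runs at z = 2.0 give a negative lower limit.

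**Step 3: an illustration on the trial's scale.** Exclusive breastfeeding stands in for the DALY effect, which cannot be simulated from the article. Inputs:
- Control prevalence is 58% (Primary research hypothesis). The difference is 5 points, read as 58% vs 63%.
- The Sampling section says "assuming an alpha of 0.05, 80% power, the estimated sample size for a two-sample proportions test would be 3200 women", with a design effect of 1.25, 20% loss and 5000 enrolled.
- Effective number: 5000 × 0.8 / 1.25 = 3200, or 1600 per arm.
- SE = √(0.58 × 0.42/1600 + 0.63 × 0.37/1600) = √(0.4767/1600) = 1.73 points.

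Results:
- The 2.5% point is reached at an observed effect of 1.96 × 1.73 = 3.4 points.
- At an observed 2 points, Φ(−2/1.73) = 12% of draws are negative. At 1 point, Φ(−1/1.73) = 28%.
- With a true 5-point effect, the chance of a non-significant estimate is Φ((3.4 − 5)/1.73), about 17%.
- The Sampling section also mentions a 35% loss through phone numbers. In place of the 20% loss it leaves 5000 × 0.65 / 1.25 = 2600 effective women and 74% power, so about 26% non-significant. Applying both losses leaves 5000 × 0.8 × 0.65 / 1.25 = 2080 and 65% power, so about 35%.
- At 2 points, with cost set to 1 unit (ratio 0.50) and an assumed 10% cost CV, the plain percentile interval is about −4.4 to +5.0.

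**Step 4: how far this carries over to DALYs.** Two checks show that it need not. Positive-only gamma draws with z = 1 give no negative effects and an interval of 0.27 to 39.5. Three independent, equally weighted effects, each with z = 1.2 (11.5% negative), combine to z = 1.2 × √3 = 2.08, with 1.9% negative.

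**The case against.** A reader might infer that the interval is meaningless for any effect that is not statistically significant. The documents do not support that. It requires draws symmetric around the estimate, and the distributions are not stated. It must also refer to modelled DALYs averted, which pool several coverage changes, so a non-significant breastfeeding result does not by itself put more than 2.5% of DALY draws below zero. Step 4 shows both escapes. Positive-only draws avoid negative ratios only by ruling out no effect or harm in advance.

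A reader might also take the Discussion as a warning that Kilkari will have no effect, because it says that "limited exposure to the program due to technological limitations in message delivery would have eroded any chance for outcome level metrics to be attained". That sentence looks back, hypothetically, at an earlier programme in Ghana. It makes a diluted effect conceivable here but is not a forecast for this trial.

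It can fairly be said that ranking dominated draws as worst is also a percentile method, and that a fuller plan may specify it. The article, however, commits to percentiles without that qualification, and plain ranking is what the words describe.

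The plane shows the spread over quadrants, the acceptability curve gives probabilities at thresholds, and the decision does not use the interval. All this stands and limits the harm. But the interval is still promised as a result, and nothing beside it changes its limits.

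Finally, plain percentile intervals covered the true ratio in about 97% of simulated trials at true z of 1, 2.8 and 4. In those cases the fault lies in what the limits mean, not in low coverage.

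**Conclusion.** The point holds in a conditional form. Plain percentiles of the simulated ratio give misleading limits when an appreciable share of simulated DALY effects is at or below zero. With symmetric draws and positive incremental cost, the lower limit turns negative at z = 1.96 for the modelled DALY effect. The upper limit is already badly understated at z = 2.0 (3.0 against about 23 to 25). At z = 2.8 the difference is small, and at z = 4 there is none.

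How likely this is cannot be computed from the article. The breastfeeding figures (12% negative draws at 2 points, about 17% of trials non-significant at a true 5 points) are illustrations. They rest on normal draws and a stand-in denominator, and the interval of −4.4 to +5.0 also rests on assumed costs. The primary effectiveness analysis and the threshold-based decision are not affected. The change is still worth making because it is nearly free and protects a figure that policy readers will quote.

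**What to change.** From the same 1000 draws, compute incremental net monetary benefit, that is, threshold × DALYs averted − incremental cost. Report its mean and 95% percentile interval at one and at three times GDP per capita. This quantity is continuous through zero effect, so its percentiles keep their order. Report it beside the planned plane and acceptability curve, with the share of draws in each quadrant.

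If an interval for the ratio is also wanted, use Fieller limits, or rank draws with higher cost and an effect at or below zero as worst, and report the upper limit as unbounded where that applies. Do not adopt a rule that allows plain percentiles when at least 97.5% of draws are positive: z = 2.0 passes it, with an upper limit of 3.0 against about 23 to 25.

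The cost is a sentence or two in the plan and one spreadsheet column, with no new data. The downside is that the reported ratio may have a less favourable or unbounded limit.
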